## Methods

### Aims of the study

The primary aim of the RCT is to assess the effectiveness of the CFTSI in reducing post-traumatic symptoms measured by the validated French version of the Child Posttraumatic Stress Checklist [18] (CPC) at 3 months after completion of the program, in children and adolescents aged 7 to 17, exposed to a TE within the last 45 days, compared to standard child-centered psychological support.

The secondary aims of the study are the following:

• To examine the effectiveness of the CFTSI in reducing post-traumatic symptoms in children and adolescents on the CPC, at 3 months after completion of the program, compared to standard child-centered psychological support.• To examine the effectiveness of the CFTSI in reducing post-traumatic symptoms in parents on the validated French version of the Posttraumatic Stress Disorder Checklist for DSM-5 (PCL-5) [19], immediately after completion of the program and at three months follow-up, compared to standard child-centered psychological support.• To investigate factors associated with the child post-traumatic symptom scores on the CPC prior to any intervention (across all included participants):
◦ Gender, age, and socioeconomic status.◦ Prior traumatic exposures measured by the adapted French version of the CPC.◦ The presence of pre-existing psychiatric or neurodevelopmental disorders measured by the validated French version of the Schedule for Affective Disorders and Schizophrenia for school-age children, Kiddie-SADS, lifetime child and parent versions, K-SADS [20].◦ The presence of one or multiple traumatic exposures in the parent, assessed using the Life Event Checklist (LEC-5) [21].◦ A lower score on the resilience measurement scale assessing social and family support and the child’s skills: Child Youth Resilience Measure (CYRM), child version (one version for ages 7–10 and another for ages 11–17) [22, 23].◦ The severity of posttraumatic reactions among parents measured by the PCL-5.◦ The type of TE.• To investigate factors associated with changes in the CPC scores post-CFTSI:

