### Trial design

The study is a single-blind effectiveness multi-site superiority RCT, comparing the telehealth delivery of the CFTSI to the online delivery of child-centred psychological support with two parallel arms and blinded assessments of the outcome measures. Outcomes on child and caregiver measures will be assessed at baseline (T0), immediately after completion of the program (T1), and 3 months after completion of the program (T2). The primary outcome point is set as T1. The Standard Protocol Items: Recommendations for Interventional Trials (SPIRIT) [24] is outlined in Table 1.

**Table 1 Tab1:** Schedule of enrollment, interventions and assesments of primary and secondary endpoints; V = visit; T = time

Visit (V)	Pre-inclusion V0 Screening T −1 to 2 weeks	Inclusion V V1 Baseline T0	Psychological Intervention 1 + 5 weeks (1 session/week for 5 weeks) ± 1 to 3 additional sessions as needed over three weeks (2 months)	Follow-up V V2 T1(immediately after completion of the program ± 7 days)	Follow-up V V3 T2 days (3 months after completion of the programs ± 7 days)
*Date*		*Day 1*		*Day 35*	*Day 185*
Protocol explanation	✓				
Oral consent		✓			
Randomization		✓			
K-SADS parents		✓			
K-SADS children		✓			
Socio-demographic questionnaire		✓			
PCL-5		✓		✓	✓
LEC-5		✓			
CPC child version		✓		✓	✓
CPC parent version		✓		✓	✓
CYRM child version		✓		✓	✓
CYRM parent version		✓		✓	✓
MFQ child version			Session 2 of the CFTSI group		
MFQ parent version			Session 1 of the CFTSI group		
PTSD-RI child version			Session 2 of the CFTSI group		
PTSD-RI parent version			Session 1 of the CFTSI group		
Family booklet			Sessions 3, 4, and 5 of the CFTSI group		
MFQ common version			Sessions 4 and 5 of the CFTSI groupCFTSI		
PTSD-RI common version			Sessions 4 and 5 of the CFTSI group CFTSI		
Developmental history			Session 1 of the CFTSI group		
THQ adapted adult and parent version			Session 1 of the CFTSI group		
THQ adapted child version			Session 2 of the CFTSI		
PCL-C *PCL-5 adapted to CFTSI			Session 1 of the CFTSI group		
Satisfaction questionnaire			Session 5 of the CFTSI group		

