### Interventions

#### The CFTSI

The CFTSI intervention consists of five to eight structured sessions, each lasting approximately 1 h, delivered at a pace of one session per week. Psychotherapists trained in CFTSI will implement the intervention solely in the experimental group, following its standardized protocol. The intervention includes Session 1, parent(s) alone; Session 2, child alone, Sessions 3–5, conjoint sessions with the child and parent(s). Additionally, one to three supplementary sessions may be conducted as needed to address specific points or review coping strategies in greater detail. The CFTSI is designed to enhance symptom recognition, improve parent-child communication, and teach targeted coping skills [10, 13–15]. The intervention focuses on key post-traumatic reaction clusters, including sleep disturbances, social withdrawal, intrusive thoughts, anxiety, anger outbursts, oppositional or aggressive behaviors, and trauma induced alterations in cognitions (e.g., guilt). A detailed CFTSI manual outlines the structure of each session, including standardized questionnaires used to assess symptom intensity, frequency, and progression over time. These questionnaires serve a dual function: they facilitate psychoeducation and improve communication around symptoms, helping both children and parents to better identify and articulate post-traumatic experiences. The CFTSI-specific questionnaires and family agenda, which records strategies learned during sessions, have been translated into French by our team. These questionnaires are fully integrated into the clinical interview and administered by clinicians within CFTSI sessions. They do not require additional effort from participants nor extra time outside of the sessions, except for the family log, which is introduced in session 3. Several questionnaires throughout the sessions serve as discussion tools. However, these are adapted clinical versions distinct from those used in blinded assessments for outcome measures. These adaptations, developed by the founders of CFTSI, have been translated into French with their consent.

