### Control group

The control group will receive five to eight weekly sessions of unstructured child-focused psychological supportive therapy conducted online. This form of supportive therapy is already part of the standard care practice at the four sites of the Occitanie regional centers for posttraumatic stress and aims to provide emotional support while strengthening the child’s daily adaptation skills. It will be delivered by psychotherapists from the Montpellier University Hospital who are not trained in CFTSI. This ensures a consistent online format, allowing for better comparability between the intervention and control groups.

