### Outcomes

We will aim to start intervention sessions no more than 2 weeks after T0 assessments, and to conduct T1 assessments on the day of the last session of the intervention. Interventions in both groups will last a maximum of 8 weeks. T2 assessments will be scheduled at 12 weeks following T1 (approximately 20 weeks after T0). In case participants do not attend a scheduled assessment, three attempts will be made to contact them in the same week, and once the following week, to schedule a new appointment. This will be done via phone calls. Interviews will be carried out on site or online by trained master-level or doctorate-level clinicians. Investigators involved in assessments will be blinded as regards program/treatment status.

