#### Analysis of primary endpoint

The analysis of the primary endpoint will be performed on an intention-to-treat basis. The primary endpoint (pre-post intervention variation in the child version of the CPC score) will be compared between the two groups using an analysis of covariance (ANCOVA) in order to adjust for the stratification criteria of the randomization. The effect size will be determined using Cohen’s d.

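### Table 1's symmetric ± 7 day window and fixed Day 35 both allow the post-programme assessment (T1) before the last session

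*Protocol article*

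**What the plan says.** - **Window and date.** Under Trial design, the T1 column of Table 1 is headed "immediately after completion of the program ± 7 days" and carries the date Day 35, with baseline at Day 1. The intervention column of the same table allows up to two months.
- **Target day.** Outcomes states the intention "to conduct T1 assessments on the day of the last session of the intervention". This is part of a sentence that begins "We will aim to start intervention sessions no more than 2 weeks after T0 assessments", so it is an aim. The same section caps both interventions at 8 weeks and puts T2 at 12 weeks after T1, about 20 weeks after T0.
- **Session spacing.** CFTSI has five to eight sessions, "delivered at a pace of one session per week", the last one to three of them given as needed. For the comparator, "The control group will receive five to eight weekly sessions".
- **Role of T1.** Trial design says "The primary outcome point is set as T1", and the analysis section describes the endpoint as the "pre-post intervention variation in the child version of the CPC score". Aims of the study places the primary comparison "at 3 months after completion of the program, in children and adolescents aged 7 to 17", and the Abstract agrees with that.

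**The concern.** A tolerance around a target visit day is routine. One that admits a post-treatment measurement during treatment is not. With weekly sessions, seven days before completion is about the day of the penultimate session. In a five-session course the visit would then come before one of the five core sessions that the article requires for full adherence. A visit booked from the tabulated Day 35 can fall earlier still relative to the end of a long or late-starting course.

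Such a visit would be within the stated window but would not measure the outcome after the programme. If the last session adds benefit, the T1 effect is understated. T1 feeds the child CPC and parent PCL-5 comparisons whichever time point is primary. It also fixes the T2 date, so an error at T1 carries forward.

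**Working it through.** **1. The plan's own sample size.** Inputs from Sample size: effect 0.53 in absolute value, power 80%, two-sided 5%. A two-sample t-test needs 56.86 per group, so 57, as stated. Power at 57 per group is 80.1%.

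**2. When the last session falls.** With session 1 on day s and no slippage, session k is on day s + 7(k − 1). The earliest start is taken as Day 1 and the latest intended start as Day 15 (2 weeks after T0).

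| First session | Session 5 | Session 6 | Session 7 | Session 8 |
|---|---|---|---|---|
| Day 1 | Day 29 | Day 36 | Day 43 | Day 50 |
| Day 15 | Day 43 | Day 50 | Day 57 | Day 64 |

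**3. Window read from completion.** Completion − 7 days is the day of session k − 1. One session is still to come.

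**4. Window read from the tabulated date.** Day 35 ± 7 is Days 28 to 42.
- With a Day 1 start, Day 35 precedes the last session of any course of 6 or more sessions (Day 36 onward). Even Day 42 precedes session 7.
- With a Day 15 start, the whole window precedes session 5 (Day 43).

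**5. Day 35 against Outcomes.** T2 at about 20 weeks after T0 and 12 weeks after T1 implies T1 at about 20 − 12 = 8 weeks after T0, or 56 days. Day 35 is about 5 weeks. Table 1 also dates T2 at Day 185, which is 185 − 35 = 150 days after its T1, against 12 × 7 = 84 days in Outcomes.

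**6. Knock-on to T2.** If T1 is 7 days early, T2 at T1 + 84 days falls 84 − 7 = 77 days after completion. Table 1 wants T2 at 3 months after completion ± 7 days. If 3 months is 91 days, the lower limit is 84 and day 77 is out of window. If 3 months is read as 12 weeks, the lower limit is 77 and the visit is just inside.

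**7. Illustrative loss of power at T1.** Assumptions, none of them from the article: the between-arm effect accrues evenly over k sessions, and a fraction f of children in both arms is assessed one session early. Then d = 0.53 × (1 − f/k). Two-sample t-test, 57 per group:

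| f | d, k = 5 | Power, k = 5 | Power, k = 8 |
|---|---|---|---|
| 0 | 0.530 | 80.1% | 80.1% |
| 10% | 0.519 | 78.5% | 79.1% |
| 25% | 0.504 | 76.0% | 77.6% |
| 50% | 0.477 | 71.4% | 74.9% |
| 100% | 0.424 | 61.2% | 69.0% |

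The article gives neither f nor the contribution of the last session. The 50% and 100% rows only mark the range; the 100% row is incompatible with the stated aim of assessing on the day of the last session.

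**The case against.** The case for leaving the text alone has four parts.

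- **Aim and tolerance.** Outcomes states an aim and Table 1 a tolerance around it. The column heading itself says that T1 follows completion, so a visit before the last session arguably fails the definition. It stands that this is an inconsistency of wording and not a hard contradiction. But the minus sign then has no legitimate use, and a site reading the table would take an early visit as allowed.
- **Late visits are what the procedure foresees.** The procedure for missed assessments runs forward only, in the same week and then the following week. That is true, and it is also a reason why the minus side is not needed. Early visits remain plausible because Day 35 is fixed while course length is not, and the extra CFTSI sessions are decided as needed.
- **Dilution is not shown.** A reader might infer that the window dilutes the treatment contrast. The documents do not support that: they give neither the share assessed early nor the effect of the last session. Even accrual is a weak assumption, since session 1 is for parents alone, session 2 for the child alone and sessions 3 to 5 are joint. In longer courses the final session is supplementary.
- **No bias between arms by design.** A reader might also infer differential timing. The window, the session range and the 8-week cap are the same in both arms, and assessors are blinded. An imbalance could arise in practice, but nothing in the article indicates one.

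**Conclusion.** The point holds as an internal inconsistency that should be corrected. Both the minus side of the window and the fixed Day 35 permit T1 before the last session, against the visit's own definition and the aim under Outcomes. This rests on the stated weekly spacing, the 5 to 8 session range and the intended start within 2 weeks.

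The effect on results is possible but not quantified. Under even accrual and one missed session, the loss of power is under 2 points if 10% or fewer are early, and about 4 points if 25% are early in five-session courses. Those figures concern the primary analysis only if T1 is the primary time point. Trial design says so, while the Abstract and Aims of the study say 3 months. That conflict is a separate matter and lends no weight here. If 3 months is primary, the consequence is an earlier T2, by up to 7 days under the completion-based reading, and a possible T2 window breach. The planned sample size does not change.

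**What to change.** Define T1 in both arms relative to each child's actual last session, with an assessment window of 0 to +7 days. In Table 1, replace ± 7 days for T1 accordingly. Remove Day 35 or mark it as indicative only, so that the table agrees with Outcomes and with courses of up to 8 weeks. Reconcile the tabulated Day 185 with the T2 rule at the same time, since T2 is counted from T1.

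The change concerns assessment timing only and leaves treatment and sample size untouched. The cost is an edit to Table 1 and slightly less flexibility for assessors. It is best made before recruitment, planned from December 2025, is far advanced.

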### Study setting

The recruitment will take place among parents seeking consultation for their children at one of the four branches of the Regional Center for Posttraumatic Stress in the Region of Occitanie in France, within 45 days of the child’s exposure to a TE. The Regional Centers for Posttraumatic Stress in France provide a comprehensive care system—including evaluation, orientation, and treatment—for individuals suffering from PTSD across all ages. These centers are affiliated with hospitals and cover all regions of France. The center in the region of Occitanie serves four cities: Montpellier, Toulouse, Nîmes, and Thuir. Both interventions (CFTSI and child centered supportive psychotherapy) will be delivered by psychologists at the University Hospital of Montpellier. Clinicians delivering the CFTSI will have received prior CFTSI training and supervision by the founders of the CFTSI. The interventions will be conducted entirely online. This approach will facilitate participation for families from centers outside Montpellier and enhance parental compliance, particularly for those facing time or transportation constraints. Recruitment will begin in December, 2025 and is expected to be completed by June 2027.

## Participants

### Eligibility criteria

Families will be included if they meet the following inclusion criteria: (i) have a child or adolescent aged 7 to 17 years living in the family home, (ii) the child has been exposed to a TE aligning with the DSM-5 criteria for TEs within the past 45 days, (iii) there is at least one symptom on the Child Post-Traumatic Stress Checklist (CPC) at T0, (iv) at least one of the parents is available to participate in the intervention, (v) being fluent in French, both orally and in writing, and (vi) no concurrent participation in other therapeutic interventions aimed at treating traumatic stress symptoms during the inclusion period.

Participants will be excluded if they meet any of the following criteria: (i) parents and/or children present an imminent risk requiring immediate case management at the time of recruitment, or severe psychiatric disturbance or risks requiring specialist mental health services. This will be assessed by a clinical evaluation while gathering consent (preinclusion) and will be based on the clinical judgment; (ii) children are in foster care or in the process of being placed; (iii) there is suspicion of maltreatment or abuse perpetrated by one or both parents; (iv) children and/or parents have a known and/or documented intellectual disability, and (v) there is an absence of informed consent from at least one parent and/or refusal of participation by the child.

### Interventions

#### The CFTSI

The CFTSI intervention consists of five to eight structured sessions, each lasting approximately 1 h, delivered at a pace of one session per week. Psychotherapists trained in CFTSI will implement the intervention solely in the experimental group, following its standardized protocol. The intervention includes Session 1, parent(s) alone; Session 2, child alone, Sessions 3–5, conjoint sessions with the child and parent(s). Additionally, one to three supplementary sessions may be conducted as needed to address specific points or review coping strategies in greater detail. The CFTSI is designed to enhance symptom recognition, improve parent-child communication, and teach targeted coping skills [10, 13–15]. The intervention focuses on key post-traumatic reaction clusters, including sleep disturbances, social withdrawal, intrusive thoughts, anxiety, anger outbursts, oppositional or aggressive behaviors, and trauma induced alterations in cognitions (e.g., guilt). A detailed CFTSI manual outlines the structure of each session, including standardized questionnaires used to assess symptom intensity, frequency, and progression over time. These questionnaires serve a dual function: they facilitate psychoeducation and improve communication around symptoms, helping both children and parents to better identify and articulate post-traumatic experiences. The CFTSI-specific questionnaires and family agenda, which records strategies learned during sessions, have been translated into French by our team. These questionnaires are fully integrated into the clinical interview and administered by clinicians within CFTSI sessions. They do not require additional effort from participants nor extra time outside of the sessions, except for the family log, which is introduced in session 3. Several questionnaires throughout the sessions serve as discussion tools. However, these are adapted clinical versions distinct from those used in blinded assessments for outcome measures. These adaptations, developed by the founders of CFTSI, have been translated into French with their consent.

#### Fidelity

To evaluate fidelity of the CFTSI to the treatment model, clinicians will complete a session checklist at each session to indicate which components were completed, which family members attended, and whether any rescheduling was needed. All sessions will be recorded and 20% of the recordings will be reviewed by a supervisor who is trained in CFTSI, who will complete a structured observation form, developed for the CFTSI, to score which elements of the intervention have been carried out by the clinician and to what quality. Additionally, regular supervision and coaching sessions will take place with experienced and trained CFTSI supervisors of the Yale Child Study Center.

### Control group

The control group will receive five to eight weekly sessions of unstructured child-focused psychological supportive therapy conducted online. This form of supportive therapy is already part of the standard care practice at the four sites of the Occitanie regional centers for posttraumatic stress and aims to provide emotional support while strengthening the child’s daily adaptation skills. It will be delivered by psychotherapists from the Montpellier University Hospital who are not trained in CFTSI. This ensures a consistent online format, allowing for better comparability between the intervention and control groups.

### Informed consent and assent (pre-inclusion)

During the pre-inclusion visit, the investigator provides detailed information to the parent(s) and child, addressing any questions about the study’s objectives, potential constraints, foreseeable risks, and expected benefits. The investigator also explains the rights of research participants and verifies the eligibility criteria. Following this discussion, the investigator provides the parent(s) with a copy of the information sheet. The child also receives age-appropriate informational materials (for ages 7–11 or 12–17) and is informed about the study procedures. The child’s personal assent is sought, and their decision is fully respected. If the child chooses not to participate, they will not be included in the study. After this information session, parent(s) are given a 3 days reflection period to make an informed decision, in order to keep the intervention as soon as possible. If they choose to participate, they give their consent orally to the investigator, which is obligatory before any clinical or paraclinical assessments related to the study are conducted. An attestation will be signed by the investigator to document these oral agreements, collected in the e-CRF for traceability and the participation will be recorded in the patient’s medical file.

### Outcomes

We will aim to start intervention sessions no more than 2 weeks after T0 assessments, and to conduct T1 assessments on the day of the last session of the intervention. Interventions in both groups will last a maximum of 8 weeks. T2 assessments will be scheduled at 12 weeks following T1 (approximately 20 weeks after T0). In case participants do not attend a scheduled assessment, three attempts will be made to contact them in the same week, and once the following week, to schedule a new appointment. This will be done via phone calls. Interviews will be carried out on site or online by trained master-level or doctorate-level clinicians. Investigators involved in assessments will be blinded as regards program/treatment status.

